**Figure 2 fig2:**
[figure not shown]
Flow diagram of anticipated allocation of adolescent participants. Note that sample sizes for allocation (*N* =  50 overall) and analysis (*N* =  40 overall) are estimated *a priori*, respectively, see section “Estimation of samples size”.

Also during the sampling stage, youth welfare institution personnel receives a newly designed one-day workshop on SUD-relevant topics. After completion of data sampling from adolescent DELTA-JU participants and personnel who evaluate the workshop, the dissemination stage starts where the DELTA-JU manual and overall evaluation results on the resulted DELTA-JU intervention are published. All measures and procedures are approved by ethics committee of the Technische Universität Dresden as an amendment to the DELTA evaluation study (approval in Jan 2022, number: EK 66022018).

#### Adjustment stage

During the adjustment stage in months 1–4, youth welfare institutions focusing on full-time housing for adolescents with SUDs are identified by contacting communal youth service authorities that typically provide long-term accommodation, in-house schooling, and psychosocial support for abstinent adolescents with SUDs. Identified institutions will receive letters or emails where study aims, procedures, and conditions are explained, asking for a collaboration. A formal cooperation agreement will be obtained with them. Institutional personnel will ask all adolescents and their legal guardians about their interest to participate, and will help to disseminate study information material. Furthermore, institutional personnel will be asked to participate in individual interviews (*n* = 10). The audio-taped interviews will take place in a separate room on an individual location to provide privacy. Interviews follow an semi-structured guideline in accordance with standards in the field of qualitative methods (25–29), with questions about the following areas of interest: (1) what are organizational challenges to implementing weekly group session in the institution (e.g., already existing therapeutic offers), (2) what session would be necessary and what problems do adolescents encounter in the institution, and (3) which needs does the personnel have regarding the one-day workshop? Responses will be analyzed with content analysis (29, 30) and/or Grounded Theory (29, 31). Thereby identified aspects in each of the three areas will be discussed by the study team so that for each aspect, at least one way how to implement it into the revision of DELTA is defined and subsequently carried out. Additionally, expert knowledge of the principal investigators will help to revise content and procedures of the manual in order to optimize its fit for the youth welfare institutional setting. The adjustment stage ends with the finally revised DELTA-JU manual including revised materials for adolescents as well as for personnel regarding the one-day workshop.

#### Sampling stage

During the sampling stage in months 5–22, adolescents will be recruited in cooperating youth welfare institutions in the study region, followed by a group-wise cluster-randomization. Adolescent participants will be prospectively assessed both at baseline (BL, a week before the intervention starts) and at follow-up (FU, 16 weeks after first group session). Those in the WL group will receive an additional pre-assessment (PRE, 16 weeks before intervention starts) for the WL to control for natural development. Assessments will take place in the youth welfare institution if possible, or in our outpatient clinic, e.g., for physical examinations. Questionnaires will be filled out in participant’s free time. Participants will be reimbursed at PRE (15 EUR), BL (20 EUR), and FU (40 EUR). The DELTA-JU group and individual sessions will be carried out as outlined below (“Interventions”) with possible changes due to the revision process. Study team members (i.e., psychologists, medical doctors, doctoral students, and student assistants from psychology, medicine, social work, or similar) who conduct the sessions or any assessment will be trained and supervised by the principal investigators.

During the same time, personnel from the youth welfare institutions will receive the revised one-day workshop on SUD-relevant topics. Workshops will be carried out either in the institutions themselves, in our outpatient clinic, in a public place, or via video conference if necessary due to restrictions for the prevention of COVID-19 infections. Whenever possible, personnel from similar institutions will be allowed to participate in the workshop. Personnel will also be assessed twice (BL at beginning and end of the workshop day, FU 16 weeks later) with questionnaires regarding the evaluation of workshop content and organization. All procedures were conducted in accordance with the Declaration of Helsinki, publicly pre-registered and approved by the local Institutional Review Board (see “Ethics” section below). For details on the dissemination stage, see "Dissemination” section below. The treatment and measurement schedule is shown in Figure 3.

**Figure 3 fig3:**
[figure not shown]
Treatment and measurement schedule for (a) adolescents and (b) youth welfare institution personnel. Timing of the 1-day workshop may vary for each institution based on time constraints of the personnel.

#### Setting and participants

Youth welfare institutions will be approached if they are in the study region (district of Saxony and, if feasible, surrounding areas in Brandenburg and Thuringia). Generally, those institutions specialized in SUD care are placed outside of metropolitan areas (32) in order to reduce risk factors for relapse (such as contact to drug dealers) (33). Adolescents and their legal guardians will be approached by personnel of participating institutions. If interested, study personnel will hand out information material and will answer all questions in person, via telephone or via e-mail. Consent will be given after additional verbal information to adolescents. Inclusion criteria for adolescents are: (1) aged 12.00–17.99 years, (2) SUD diagnosis, or (3) chronic substance use during the past. The only exclusion criterion is low cognitive functioning (intelligence quotient <70). For BL-FU analyses, we will not analyze participants who did not attend any of the 16 sessions for whatever reason or if study participation was discontinued due to an adverse event. Participants choosing to discontinue are immediately asked whether they want to provide data on primary outcomes anyhow. Personnel of youth welfare institutions is included if they work with at least 20 h/week in a cooperating institution. The anticipated flow of adolescent participants is shown in Figure 2. At the time of writing this protocol, study registration is completed (01. Feb 2022) and the first adolescent participants are being recruited, randomized, and enrolled (starting 02. Feb 2022).

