#### Additional measures

Current DSM-5 diagnoses for SUDs as well as co-occurring mental disorders are assessed with the Mini-International Neuropsychiatric Interview for Children and Adolescents (MINI-KID) (35) or the Childrens’ Diagnostic Interview for Mental Disorders (C-DIPS) (61, 62) depending on license availability. Both instruments are structured interviews for DSM-5 disorders in children and adolescents with substantial to almost perfect interrater and test–retest reliability (35, 61).

Sociodemographic characteristics of adolescents are acquired via questionnaire from legal guardians, including information on participant’s age (in years), gender, parental school education (list of school graduation options), and relationship status of biological parents. Sociodemographic characteristics of personnel is obtained via standardized questions regarding age (in years), gender, school education (list of school graduation options), and current SUD-related subjective utility (percentage, from 0 = ‘none at all’ to 100 = ‘all you must know’).

Adherence to therapy is operationalized through the number of sessions attended by each adolescent (ranging from 1 to 16 sessions, with more sessions indicating stronger adherence) and by subjective rating of active participation by each adolescent itself (five-item questionnaire, GTS-P) (34). Although participants are instructed to attend to all 16 weekly sessions as well as individual sessions, thus only participants with one or more attended sessions will be analyzed. The study team member who conducts a group session will additionally rate how well the group participated actively in each respective session, and whether any adverse events occurred (nine-item questionnaire, GTS-T) (34). Drop-out from the study as well as discharge of adolescents from an institution will be recorded by study personnel.

Substance use motives specifically for smoking are assessed via the Motives Questionnaire Revised for Smoking (MQ-RS), an instrument we developed. The MQ-RS uses the 20 items and the five-point scale [ranging from 1 = (almost) never to 5 = (almost) always] from the established drinking motives measure of Cooper in its revised form (45). In contrast to drinking motive measure, we had to reword items 8 (“…about not smoking” instead of “…about not drinking”) and 10 (“…to feel the kick” instead of “…to get high”) in order to avoid alcohol-specific or smoking-unrelated wording.

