### Data analysis

Analyses will be conducted with the most recent version of the software “IBM SPSS Statistics,” currently version 27.0. Adolescents are analyzed as randomized if they participated in at least one DELTA session (DELTA condition only). To test all non-descriptive hypotheses (see below, hypotheses 2–4), a repeated measures MANOVA will be conducted using time as factor (“within factor”) given the explanatory nature of the trial and the non-importance of between-group effects. A significant reduction over time (BL vs. FU) in all *N* = 40 participants across all metric outcomes (MaCS score, FTND score, DUDIT score, AUDIT score, and cigarettes per day during the past month according to substance use interview) indicates a relevant intervention effect. This multivariate approach will limit the chance for false-positive results as otherwise possible due to multiple testing. Effect sizes will be classified into small effects (ƞ^2^ ≥ 0.01), medium effects (ƞ^2^ ≥ 0.06), and large effects (ƞ^2^ ≥ 0.14). In case of severe non-normality of outcome variables, we will have to apply non-parametric tests instead of the repeated measures MANOVA.

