#### Hypotheses

Aim (A) is reached when for each need, identified through qualitative analyses of interviews, one or more adjustments to the content or procedure of DELTA-JU is documented. No quantitative hypothesis is applicable. Aims (B) and (C) are achieved through testing the following hypotheses in adolescents who are abstinent for alcohol and drugs except nicotine/tobacco:
Adolescents: relevant increase in SUD-related subjective utility through FU (descriptive: a medium rating of 2.0 or higher in the respective GEJ items across participants);Adolescents: significant reduction of substance-related craving as a measure of relapse risk (*p* < 0.05, MaCS score) through FU;Adolescents: significant reduction of SUD severity (*p* < 0.05, scores of FTND, AUDIT, and DUDIT) through FU;Adolescents: significant reduction of self-reported past-month tobacco use through FU (*p* < 0.05, substance use interview);Personnel: relevant increase in SUD-related subjective utility through FU (descriptive: a medium rating of 2.0 or higher in the respective GEB items across participating personnel); andPersonnel: high satisfaction ratings concerning the workshop organization (descriptive: a medium rating of 4.0 or higher in the respective GEB items across participating personnel).

Additionally, secondary outcomes in adolescents (BDI-II, PQ-16, UCLA-PTSD, PSS-10, and SWLS) and personnel (ERI-S-10) will be tested exploratorily for changes through FU as previously done in the DELTA evaluation (15). All reductions through FU in adolescents are expected to be descriptively larger than reductions over the natural course, i.e., from PRE to BL in the WL group.

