### Strengths and limitations

The presented study design has several strengths. First, it is in line with ethical requirements that all adolescents are offered treatment. Waiting for 16 weeks in the WL condition still seems adequate given that adolescents may reside for up to 2 years in youth welfare institutions. In randomized clinical trials, for example, only cases may have received treatments. Second, it requires a smaller sample when participants become part of several analysis groups (intervention vs. WL). Third, alternative explanations of time effects may be controlled for by comparing BL-FU effects with PRE-BL effects.

Challenges arise from uncontrolled parallel treatments during the waiting period. Such treatments cannot be included in the quantitative estimation of treatment effects due to the limited number of participants in each group. Furthermore, homogeneity of cooperating youth welfare institutions is limited. Results may thus have to be replicated in other and diverging institutions. Although the sample size was *a-priori* calculated to maximize the use of available resources, drop-out rates may be unexpectedly high. In this case, additional participants and institutions may have to be recruited. In case of limited sample size, using Bayesan methods instead of testing for differences from zero may be advisable (74). Both the AUDIT and DUDIT have been previously used to assess changes in alcohol- and drug-related problems in adolescents and young adults using 3-month intervals between BL and FU (75, 76). Nevertheless, it remains possible that small changes in problems might go unnoticed given that both instruments cover 12 month periods. Another limitation arising from the limited sample size in a phase II study is the impossibility to adjust for several baseline variables. Such superior analysis strategies are not feasible at this point of the intervention development but will be imperative during phases III/RCT and phase IV studies in the future. The same holds true for the analysis of relevant patient subgroups (e.g., differentiating those with primarily alcohol-related problems from those with primarily cannabis-related problems) and intention-to-treat analyses or sensitivity analysis. Finally, additional measures that would objectify relapse to the use of alcohol or other drugs were not funded and will have to be implemented in a future trial, preferably a multi-center RCT testing DELTA-JU against treatment-as-usual.

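### The BL-FU analysis set excludes adolescents on post-baseline events, is defined differently in different sections, and is not 'as randomized'

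*Protocol article*

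**What the plan says.** Three sections of the protocol article say who is analysed.

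- **Setting and participants** gives two grounds for leaving an adolescent out of the BL-FU analyses, namely that they "did not attend any of the 16 sessions for whatever reason or if study participation was discontinued due to an adverse event".
- **Additional measures** repeats the attendance ground alone: "thus only participants with one or more attended sessions will be analyzed".
- **Data analysis** states: "Adolescents are analyzed as randomized if they participated in at least one DELTA session (DELTA condition only"). The adverse-event ground does not appear there.

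Four other statements bear on the point.

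- Setting and participants also provides: "Participants choosing to discontinue are immediately asked whether they want to provide data on primary outcomes anyhow".
- The deciding test under Data analysis is within person: "a repeated measures MANOVA will be conducted using time as factor". It compares BL with FU in all 40 analysed adolescents, pooled over arms.
- Hypotheses sets a benchmark: "All reductions through FU in adolescents are expected to be descriptively larger than reductions over the natural course". The natural course is the PRE-to-BL change in the waitlist group.
- Strengths and limitations lists "intention-to-treat analyses or sensitivity analysis" among the strategies it calls infeasible in this phase, in an argument that starts from the limited sample size.

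**The concern.** An adverse event that ends participation occurs after baseline and may be a consequence of the intervention. Removing those adolescents from the efficacy estimate can remove people in whom the intervention went badly. Attending no session is a different kind of selection: it is on adherence, not on outcome, although adherence and outcome may be related.

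The main result is a single pooled pre-post change, so any selection related to that change shifts the estimate directly. A reader who sees the set described as analysed as randomized would not expect an adverse-event exclusion. Two analysts following different sections could also arrive at different data sets.

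**Working it through.** **1. The plan's own figure.** Estimation of sample size gives f = 0.40, r = 0.1, alpha 0.05 and power 0.95. With two time points (m = 2), the noncentrality is f² × n × m / (1 − r). At n = 40 this is 0.16 × 40 × 2 / 0.9 = 14.22, and power is 0.957. The smallest n reaching 0.95 is 39 (power 0.952). Allowing 20% dropout, 40 / 0.80 = 50. The stated 40 and 50 are reproduced. The sample size is not at fault; the issue is which of the 50 are analysed.

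**2. The rules side by side.** Take an adolescent who has both BL and FU data.

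| Case | Setting and participants | Additional measures | Data analysis |
|---|---|---|---|
| At least one session, no adverse-event discontinuation | in | not excluded | in |
| At least one session, discontinued for an adverse event | **out** | not excluded | **in** |
| No session | out | out | out in the DELTA condition |

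The second row is a direct conflict. In the third row, the bracketed restriction under Data analysis leaves unclear whether waitlist adolescents are covered once their own sessions begin. Setting and participants covers every BL-FU analysis.

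**3. Form of the bias.** Let N adolescents have a BL-FU change and let k of them be excluded. Then:

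reported gain − gain in all N = (k / N) × (mean gain of retained − mean gain of excluded).

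This is zero when the two groups change equally, positive when the excluded do worse and negative when they do better. The documents give neither k nor the difference. Assumed example: 40 retained gain 0.50 SD and 4 are excluded.

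- Excluded also gain 0.50 SD: no overstatement.
- Excluded do not change: 40 × 0.50 / 44 = 0.455 SD in all, so 0.50 is 10% too large.
- Excluded worsen by 0.50 SD: (40 × 0.50 − 4 × 0.50) / 44 = 0.409 SD, so 0.50 is 22% too large.

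**4. Effect on the test.** A simulation assumed 50 enrolled, no true change, one normally distributed outcome, a two-sided paired t test at 5% and 40,000 runs. The k adolescents with the highest exclusion score were removed; that score has correlation rho with a worse change. Each cell gives the spurious improvement in SDs of change, then the rejection rate.

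| Excluded of 50 | rho 0 | rho 0.25 | rho 0.5 | rho 1 |
|---|---|---|---|---|
| 2 | 0; 5.0% | 0.02; 5.3% | 0.04; 6.5% | 0.09; 11.5% |
| 5 | 0; 5.1% | 0.05; 6.1% | 0.09; 10.5% | 0.19; 33.2% |
| 10 | 0; 5.0% | 0.09; 8.4% | 0.17; 21.0% | 0.34; 74.9% |

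Ten is the whole 20% dropout allowance (50 − 40). The column rho = 1 is an extreme. The plan's test is multivariate over five outcomes, so these rates show the mechanism and do not predict this trial.

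**5. The infeasibility statement.** Including adolescents who have FU data but are now excluded raises the analysed number. A limited sample size therefore cannot be the reason for leaving them out.

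**The case against.** The case for the plan has real weight.

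- **The attendance rule is open.** It stands in the same sentence as the description of the set, and that description may mean only analysis by allocated group, as in a modified intention-to-treat set. This holds for attendance. It does not cover the adverse-event exclusion, which that sentence omits.
- **The limitation is disclosed.** The article says it will have no intention-to-treat analysis. But the disclosure does not mention the adverse-event exclusion or its possible direction, and the reason it gives does not hold.
- **Few may be affected.** Sessions take place on site and fit the institution's schedule, so zero attendance may be rare, and it may reflect discharge rather than a poor course. No count is given either way.

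A reader might also infer more than the documents support:

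- *That the filter breaks the randomized comparison or is stacked against the waitlist.* The deciding test has time as its only factor, and between-group effects are set aside. No attendance filter could operate in the waiting period, because there are no sessions in it. Setting and participants applies the rule to waitlist adolescents in their own BL-FU period. What remains is narrow: the PRE-BL benchmark is not limited to the same adolescents, and that comparison is only descriptive.
- *That the missing data are already in hand.* The request for primary-outcome data goes to those who choose to discontinue, and is made immediately. The article does not say that it extends to adverse-event discontinuations or to the FU time point.

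**Conclusion.** The point holds in limited form. The sections define different BL-FU sets, and neither is as randomized: one conditions on attendance, the other on attendance and on not having been discontinued for an adverse event. The adverse-event exclusion is the harder to defend, because treatment may have caused the event. The no-session exclusion selects on adherence.

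It would be too strong to say that the set is selected on treatment outcome throughout, or that the reported change is overstated. Overstatement requires that excluded adolescents do worse, which is plausible but not shown. In the assumed scenarios, the spurious improvement runs from zero to 0.19 SD of change with 5 of 50 excluded, and from zero to 0.34 SD with 10 excluded. No single figure follows from the documents.

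**What to change.** - Reconcile Setting and participants, Additional measures and Data analysis into one definition, and make clear how it applies to the waitlist arm.
- Remove the adverse-event exclusion.
- Make the main BL-FU analysis all allocated adolescents with a BL assessment, using every FU outcome obtained, including from those who discontinued for any reason. Define BL as the pre-intervention assessment in each arm: Table 1 places it at week 17 for the waitlist, while Table 3 labels baseline week 0.
- State whether the request for primary-outcome data also covers adverse-event discontinuations.
- Keep 'at least one session attended' as a secondary set under that name, and show the PRE-BL comparison for the same adolescents.
- Report exclusions and missing FU by reason and arm.
- Delete the statement under Strengths and limitations that sample size rules out intention-to-treat or sensitivity analyses.

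The cost is mostly wording, with no additional participants. This point does not require replacing the MANOVA with another model. The estimated change may be slightly smaller, and FU data may be missing for some who discontinued; that number should be reported.

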### Interventions

#### DELTA intervention before revision

The manualized DELTA intervention (12) aims to reduce substance use and SUD-related problems to obtain abstinence and general well-being. It combines motivational interviewing, contingency management, cognitive-behavioral, and systemic therapy, see Table 2. Weekly group sessions of 60-min with 3–8 adolescents are led by up to two psychologists, who also conduct up to eight individualized 1-on-1 sessions (30 min) for each participant. Group sessions follow a structured plan including recurring elements (past-week craving review, checking homework, setting session goals, session-specific content, getting new homework, mindfulness exercise or reflection and feedback, and sporadic urine testing) and session-specific work sheets, but it also includes role plays, presentations, white-board actions, written self-evaluations, experimentation with skills boxes, mindfulness exercises etc. Attendance of all sessions is required and formally accepted within a signed “therapy contract.” Exemptions from sessions need an *a-priori* explanation (e.g., doctor’s appointment). When two or more meetings were missed without a valid explanation, or a sporadic drug urine test was positive on two occasions, adolescents have to be temporally excluded from group sessions for 8 weeks. Re-entry into the group sessions was possible after 8 weeks or a consultation with the attending therapist.

**Table 2 tab2:** Intervention content of the DELTA intervention before revision.

Session	Topic	Goal(s)
Adolescent patients group		
1.	Use and motivation to stop	Link substance use to SUDs Discover personal abstinence motivation
2.	Triggers	Identify triggers for craving and relapse
3.	Skills	Explore anti-craving skills
4.	New challenges	Develop situational anti-relapse strategies
5.	Relapse and stress	Reduce stress to prevent relapses
6.	Self-esteem	Develop self-esteem
7.	Honesty	Develop honesty in substance use self-reports
8.	Depression	Prevent and cope with depressiveness
9.	Boredom	Prevent and cope with boredom
10.	Understanding emotions	Identify emotions and associated reactions
11.	Coping with emotions	Promote activities to evoke positive emotions Avoid activities/situations associated with negative emotions
12.	Relapse justifications	Avoid situations with relapse risk
13.	Anti-relapse training	Revisit relapse prevention strategies, especially “3. Skills”
14.	Setting personal limits	Respect needs and limits of self and others learn to say “yes” and “no” if adequate
15.	Alcohol	Understand alcohol as a risky drug
16.	Review (*or optional: s*hifting addictions)	Evaluate own progress understand that excessive use of other substances or media or internet puts oneself at risk for future disorders
Parental education group		
1.	SUDs^a^	Understand SUD development
2.	Substances^a^	Understand effects of different psychoactive substances
3.	Recovering families^a^	Understand SUD treatment stages
4.	Relapse^b^	Accept relapse as possible part of recovery Develop strategies when relapse occurs
5.	Living with addiction^b^	Reflect child–parent relationship reflect own parental style
6.	Communication^b^	Reflect own communication behavior Develop alternative strategies for problematic communications
7.	Nonviolent communication^b^	Develop and train basic principles of nonviolent communication
8.	Self-care^b,c^	Understand necessity to take care of oneself Reflect on other family members/siblings

SUD, substance use disorders. ^a^based on a digital presentation; ^b^based on work sheets and material for multi-parent exchange; and ^c^an optional ninth session with individual topics may be offered.

